### Outcome measures and progression criteria

The schedule of data collection is shown in figure 3 (the SPIRIT figure).

**Figure 3 F3:**
[figure not shown]
Standard Protocol Items: Recommendations for Interventional Trials (SPIRIT) figure—schedule of enrolment, intervention and data collection. SCEPTRE, promoting smoking cessation and preventing relapse to tobacco use following a smoke-free mental health inpatient stay.

### Primary feasibility outcomes

The primary outcome of this feasibility trial will be to assess whether prespecified progression criteria are met to progress to the full randomised trial of the SCEPTRE intervention. Progression criteria are based on participant recruitment, retention, number of Trusts enrolled and the feasibility of collecting CO readings (table 2). Recruitment and retention will be assessed through screening data and retention rates tracked throughout the study duration; compliance with the protocol will be monitored using self-assessment checklists completed by MTSs and reported protocol deviations. Depending on whether primary criteria are met, the level of contamination and suitability of the randomisation approach will be examined through qualitative data collected at 3 months post-randomisation and quantitative data from control participants at 3 and 6 months post-randomisation; and additional acceptability measures will be gathered via semistructured interviews with both control and intervention group participants at 3 months post-randomisation. Furthermore, the feasibility of collecting CO readings will be assessed alongside these measures.

**Table 2 T2:** SCEPTRE feasibility study progression criteria

Progression criterion	Target at end of internal pilot	Green (progression to full RCT without major modifications)	Amber (progression to full RCT may be possible with modifications)	Red (full RCT not feasible)
Participant recruitment	64 Participants recruited	100% (64)	60%–99% (38–64)	<60% (<38)
Participant retention(primary outcome data available at 6 months)	At least 80%	80%–100% (51–64)	60%–80% (38–51)	<60% (<38)
Trusts enrolledeach Trust expected to provide 1–2 sites/wards (can be more)	8	80%–100% (6–8)	60%–80% (5–6)	<60% (<5)
Feasibility of collecting carbon monoxide reading (biochemically validated primary outcome measure)	CO reading collected for at least 75% of all participants (intervention and control group) reporting to be abstinent	75%–100% (absolute figures to be confirmed)	50%–75%	<50

CO, carbon monoxide; RCT, randomised controlled trial; SCEPTRE, promoting smoking cessation and preventing relapse to tobacco use following a smoke-free mental health inpatient stay.

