**Methods and analysis:**

This feasibility study will be an individually randomised, controlled trial in eight National Health Service mental health Trusts recruiting adults (≥18 years) admitted to an acute adult mental health inpatient setting who smoke tobacco on admission, or at any point during their inpatient stay. Consenting participants will be randomised to receive a 12-week intervention consisting of components aimed at promoting or maintaining positive smoking-related behaviour change following discharge from a smoke-free mental health inpatient setting or usual care. Data will be collected at baseline, 3 months and a second timepoint between 4 and 6 months post-randomisation. With 64 participants (32 in each group), the trial will allow a participation rate of 15% and completion rate of 80% to be estimated within a 95% CI of ±3% and ±10%, respectively. The analysis will be descriptive and follow a prespecified plan.

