#### Informed consent and data collection

Consent will be obtained in-person or remotely via telephone/video call. All participants will have received a copy of the participant information sheet at least 24 hours prior to obtaining consent. The consent form will also contain optional statements in relation to consent to interview for the qualitative aspect of the study.

Once participant eligibility has been confirmed and consent obtained, participants will be asked to complete a baseline questionnaire. If required, consent procedures and collection of baseline data can be separated into two visits dependent on participant preference. Data will be collected either using bespoke case report forms (CRFs) completed electronically via the secure web-based outcome data collection interface ‘REDCap’, over the telephone with a SCEPTRE researcher, or collected on paper CRFs returned via free post envelopes to York Trials Unit (YTU). All reporting of data collection will be undertaken in line with the CONSORT statement.^21^ The baseline assessment includes sociodemographic information as well as information on mental and physical health and smoking history and behaviour. Participants who self-report they have not smoked will be asked to provide an expired air carbon monoxide (CO) reading. We will ask participants for full contact details at baseline (including mobile phone number, email and address) and any contact preferences.

After the baseline assessment is completed, a member of the Trust’s research team will randomise participants to either the intervention or comparison group. All participants (intervention and control) will be followed up for the purposes of the study via self-completed questionnaires at 3 months and 4–6 months post-randomisation to accommodate a variable second follow-up period which allows us to extend the recruitment period without extending the duration of the study overall. During the follow-up, outcome measures to be collected include smoking-related measures and mental and physical health measures. While completing the follow-up questionnaires, participants who self-report that they have not smoked in the previous 7 days will be invited to undertake a CO measurement to validate their abstinence from tobacco. Participants who decline the invitation will be asked to provide a reason for declining, and this will be recorded on the questionnaire.

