### Proposed trial outcome measures

All participants will be asked to complete follow-up questionnaires with a member of the research team at 3 and either 4, 5 or 6 months post-randomisation (see figure 3).

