#### Mental and physical health measures

The 9-item Patient Health Questionnaire depression scale,^32^ the Generalised Anxiety Disorder 7-item scale^33^ and the quality-of-life scale (EuroQol- 5 Dimension (EQ-5D))^34^ will be included. Frequency of use of health services (health economic data) since discharge will also be collected.

We will review the suitability and definitions of the two core smoking-related outcome measures, as per current debate in the field,^35^ as follows: for 7-day point prevalence abstinence, we will review and potentially adjust downward the CO threshold of <10 ppm for biochemical validation, depending on the suitability of this approach for our patient population; for the multiple continuous abstinence outcome measures (1–6 months), we will review the availability and congruency of data and define one consistent secondary outcome measure accordingly.

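### The retention progression criterion is set at 6 months for all 64 participants, but the schedule gives each participant a single second follow-up at 4, 5 or 6 months

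*Protocol article*

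**What the plan says.** The primary outcome of this feasibility trial is whether the progression criteria in Table 2 (Primary feasibility outcomes) are met. The retention row reads "Participant retention(primary outcome data available at 6 months". Its bands are Green 80%–100% (51–64), Amber 60%–80% (38–51) and Red below 60% (fewer than 38). Red is labelled as meaning that the full RCT is not feasible.

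The follow-up schedule is described differently everywhere else:

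- Abstract, Methods and analysis: "Data will be collected at baseline, 3 months and a second timepoint between 4 and 6 months post-randomisation".
- Informed consent and data collection: the second questionnaire falls at 4–6 months, and the variation is deliberate, "to accommodate a variable second follow-up period which allows us to extend the recruitment period without extending the duration of the study overall".
- Proposed trial outcome measures: questionnaires "at 3 and either 4, 5 or 6 months post-randomisation (see figure 3".
- Level of contamination and suitability of randomisation approach, and the health economic text under Data analysis: again 3 months and then one of 4, 5 or 6 months.

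The text above Table 2 has a second fixed 6-month reference. It plans contamination data as "quantitative data from control participants at 3 and 6 months post-randomisation", whereas the contamination section gives the variable second timepoint for the same assessment.

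**The concern.** A participant whose second follow-up is set at 4 or 5 months cannot supply data at 6 months. The article does not say whether that person counts as retained, counts as lost or leaves the denominator, and it does not say that 6 months stands for the last scheduled visit.

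The criterion feeds a go/no-go decision, and the choice of reading can change the band. The literal reading could produce an Amber or Red result from the schedule alone. The lenient reading could report, under a 6-month label, a retention figure partly obtained at 4 or 5 months. If the choice is left until the data are in, it would be made with the result in view.

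**Working it through.** **Inputs**

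- N = 64, completion rate 80%, stated precision ±10% (Sample size considerations).
- Retention cut-offs 51 and 38 (Table 2).
- Number scheduled before 6 months, *e*: not given. It is treated as unknown and varied.

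**Step 1. Reproduce the plan's figures.** The half-width is 1.96 × √(0.80 × 0.20 / 64) = 0.098, which agrees with the stated ±10%. The cut-offs are 0.80 × 64 = 51.2 and 0.60 × 64 = 38.4, printed as 51 and 38. The printed counts therefore use all 64 as denominator.

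**Step 2. Literal reading.** Only the 64 − *e* participants scheduled at 6 months can count. With independent 80% completion, the number retained is X ~ Binomial(64 − *e*, 0.80). The maximum is 64 − *e* and the expected value is 0.80 × (64 − *e*). Green is taken as X ≥ 51 and Red as X < 38.

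| Scheduled early, *e* | Maximum X | Expected X (% of 64) | P(Green) | P(Red) |
|---|---|---|---|---|
| 0 | 64 | 51.2 (80%) | 0.60 | <0.001 |
| 6 (about 10%) | 58 | 46.4 (72.5%) | 0.08 | 0.003 |
| 13 (about 20%) | 51 | 40.8 (64%) | about 0.00001 | 0.13 |
| 14 | 50 | 40.0 (62.5%) | 0 | 0.19 |
| 16 (25%) | 48 | 38.4 (60%) | 0 | 0.36 |
| 18 (28%) | 46 | 36.8 (57.5%) | 0 | 0.59 |
| 32 (50%) | 32 | 25.6 (40%) | 0 | 1 |

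With *e* ≥ 14 the maximum is at most 50, so Green cannot be reached even with no dropout. With *e* ≥ 27 the maximum is at most 37, so the result is always Red.

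**Step 3. Lenient reading.** If the final visit counts whenever it is scheduled, all 64 can contribute. Expected retention is 0.80 × 64 = 51.2 and the 51 and 38 cut-offs stand. The result is then a mixture of retention at 4, 5 and 6 months. If a participant lost by 4 months stays lost, retention cannot rise with time, so the mixture is at least as high as 6-month retention. The documents give no figure for loss between 4 and 6 months, so the size of any overstatement cannot be calculated.

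**Step 4. A third reading.** Restricting the denominator to those scheduled at 6 months would suit the label, but it contradicts the printed counts, which run up to 64. Under none of the three readings do the label, the counts and the schedule all agree.

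**The case against.** The strongest reply is that the literal reading is not the natural one. The article describes a variable second follow-up consistently outside this section, says that it is deliberate, and prints retention counts that make sense only if all 64 can contribute. On that view, 6 months in Table 2 is shorthand for the last scheduled visit and the defect is a mislabelled timepoint. This is plausible, and the fix below adopts that meaning. But the article does not say so, Figure 3 is not shown, and the shorthand still attaches a 6-month label to shorter follow-up.

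A reader might also infer several stronger points that the documents do not support:

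- **That the criterion must fail.** This depends on the unstated number scheduled early. Green is strictly impossible only from 14 of 64 upwards, and only on the literal reading.
- **That more than 25% scheduled early gives Red.** This takes an expected value for an outcome. At 16 early (25%) P(Red) is 0.36. At 18 early (28%) it is 0.59.
- **That later-opening Trusts get shorter follow-up.** The article describes no staggered opening and gives no rule for assigning 4, 5 or 6 months.
- **That 6-month continuous abstinence is a further defect.** The article already plans, "for the multiple continuous abstinence outcome measures (1–6 months"), to review data availability and settle on one consistent secondary measure.
- **That retention at 3 months goes unreported.** Retention is to be tracked throughout, shown in a CONSORT diagram, and accompanied by the amount of missing data at each timepoint.

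**Conclusion.** The inconsistency is real and lies within the trial's primary outcome. The retention criterion names a timepoint that the schedule does not give to everyone, while its cut-offs assume that everyone can contribute.

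On the literal reading, with 80% completion and independent outcomes, a small early-scheduled group is enough to make Green unlikely: 0.08 with 6 of 64, against 0.60 with none. On the lenient reading the bands work as printed, but the figure is not 6-month retention and, given cumulative loss, can only equal or exceed it.

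The split between 4, 5 and 6 months is not stated, so no single figure for the effect can be given. No bias between the arms is shown, and the article plans no direct comparison between groups. The point concerns the definition of the criterion and how its result may be used.

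**What to change.** 1. In Table 2, define retention as primary outcome data obtained at the participant's scheduled final follow-up (4, 5 or 6 months), out of all randomised. Keep the 51 and 38 cut-offs.
2. Report retention by scheduled month, each with a 95% CI.
3. State that the pooled figure may overstate 6-month retention when it is used to plan the full RCT. The estimate among those scheduled for 6 months is closer to the target, but it has a wider interval and may not come from a representative subset, so it should not be the sole basis for planning.
4. In the text above Table 2, bring the contamination timepoints into line with the variable second follow-up in Proposed trial outcome measures and in the contamination section.

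The cost is a few words in Table 2 and the text above it, one extra table and a sentence of interpretation. No additional data collection is needed. The definition should be settled before retention is assessed against the bands.

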### Sample size considerations

The feasibility study will be conducted across approximately 12 acute adult mental health inpatient wards of the participating eight Trusts. Based on combined monthly discharge figures of ~200 patients, of which we estimate conservatively that ~140 will be eligible to participate, a smoking prevalence of ~60%, and a conservative estimate of willingness of patients who smoke tobacco to take part of 20%, we will aim to recruit a minimum of 64 patients, who will be individually randomised, at a 1:1 ratio, to the SCEPTRE intervention or the control arm. A trial of this size^36^ will also allow a participation rate of 15% and completion rate of 80% to be estimated within a 95% CI of ±3% and ±10%, respectively.^37^

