### Data analysis

A statistical analysis plan giving details of the planned analyses will be drafted before data collection has been completed and reviewed by the Programme Management Group (PMG) and PSC. A brief description of the planned analyses is given below.

The statistical analysis will be carried out by a statistician based in YTU, using Stata V.17 or later. The reporting of this trial will follow CONSORT guidelines for pilot and feasibility trials.^21^ A flow diagram will be produced, depicting the flow of patients through the trial. The number of patients screened, eligible, consenting and randomised will be summarised, with reasons for ineligibility and non-consent given where available. Baseline data will be summarised descriptively by randomised group, with no formal statistical comparisons being undertaken.^39^ Continuous variables will be summarised using descriptive statistics, while categorical variables will be summarised using counts and percentages. Descriptive statistics will summarise participant outcomes by randomised group and timepoint, including the amount of missing data. Relevant measures of recruitment and retention will be calculated and compared against the pilot progression criteria. The recruitment rate will be estimated and presented alongside a corresponding 95% CI. Measures of contamination and participant engagement with the multiple components of the intervention will be summarised descriptively.

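### Table 2's rounded counts contradict its percentage cut-offs at 51 or 38 retained, 38 recruited and 6 Trusts, and the protocol does not say which form decides

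*Protocol article*

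**What the plan says.** Under Primary feasibility outcomes, the protocol article states: "The primary outcome of this feasibility trial will be to assess whether prespecified progression criteria are met". Table 2 then sets the criteria. Reading Green, Amber, Red in order, three rows pair a percentage with a count:

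- Recruitment (target "64 Participants recruited"): "100% (64) 60%–99% (38–64) <60% (<38".
- Retention (target 80% or more with primary outcome data at 6 months): "80%–100% (51–64) 60%–80% (38–51) <60% (<38".
- Trusts (target 8): "80%–100% (6–8) 60%–80% (5–6) <60% (<5".

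The carbon monoxide row has percentages only and leaves its counts to be confirmed.

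Green means going on to the full trial without major changes, Amber means that it may be possible with changes, and Red means that it is not feasible. On how results are to be set against the table, the Data analysis section says only: "Relevant measures of recruitment and retention will be calculated and compared against the pilot progression criteria". Neither section says whether the percentage or the count decides.

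**The concern.** A progression rule should return one colour for each possible result. Here the count bands overlap at some values and disagree with the percentage bands at others, so the same result can carry two verdicts. Because these criteria are the primary outcome, the choice between the two would be made after the result is known.

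The stakes differ by boundary. At 51 retained or 6 Trusts the question is Green or Amber: whether the full trial goes ahead largely unchanged or needs modification. At 38 recruited or 38 retained it is Amber or Red: whether a full trial is called feasible at all.

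**Working it through.** **Inputs.** Target of 64 participants and 8 Trusts; cut-offs of 80% and 60% (all from Table 2). Planned completion rate of 80% (Sample size considerations: "completion rate of 80% to be estimated within a 95% CI of ±3% and ±10%, respectively").

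**Step 1: reproduce the printed counts.** Cut-off × target, rounded to the nearest integer:

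| Cut-off × target | Exact | Printed count | Smallest count that reaches the cut-off |
|---|---|---|---|
| 0.80 × 64 | 51.2 | 51 | 52 |
| 0.60 × 64 | 38.4 | 38 | 39 |
| 0.80 × 8 | 6.4 | 6 | 7 |
| 0.60 × 8 | 4.8 | 5 | 5 |

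All four printed counts are reproduced. A count needed to reach a given percentage has to be rounded up. Three of the four were rounded down.

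**Step 2: grade every possible result both ways.** Results from 0 to 64 participants and 0 to 8 Trusts were classified by percentage and by count. The two forms differ only here:

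| Result | Percentage | Colour by percentage | Colour by count |
|---|---|---|---|
| 51 retained | 51/64 = 79.7% | Amber | Green and Amber |
| 38 retained | 38/64 = 59.4% | Red | Amber |
| 38 recruited | 38/64 = 59.4% | Red | Amber |
| 64 recruited | 64/64 = 100% | Green | Green and Amber |
| 6 Trusts | 6/8 = 75% | Amber | Green and Amber |

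The entry at 64 recruited is a slip for 63 (63/64 = 98.4%): the Amber percentage stops at 99% and Green is exactly 100%, so the intent is clear. The other four are real conflicts. With 64 randomised, they affect 2 of 65 possible retention results and 1 of 9 possible Trust results. One recruitment result is affected, leaving aside the misprint.

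**Step 3: how likely is a boundary retention result?** Exact binomial with n = 64, P(X = k) = C(64, k) p^k (1 − p)^(64 − k):

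| True retention p | P(51 retained) | P(38 retained) |
|---|---|---|
| 85% | 6.4% | not computed |
| 80% (planned) | 12.3% | 0.008% |
| 75% | 8.3% | 0.24% |
| 70% | not computed | 2.0% |
| 60% | not computed | 10.1% |

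At p = 80%, 51 and 52 are equally likely and are the two most likely counts. At p = 60%, 38 and 39 are likewise equal. The documents give no basis for a probability of 38 recruited or of 6 Trusts.

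**Step 4: retention when the number randomised is not 64.** The retention counts match the percentages only at or near n = 64.

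- With 60 randomised, 80% is 48, so 48 to 50 retained is Green by percentage and Amber by count.
- With 50 randomised, 80% is 40, while the printed Green count of 51 cannot be reached.

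Amber recruitment allows such totals.

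**The case against.** The table can be read as making the percentage primary. It comes first in every row, with any count in brackets. The carbon monoxide row fixes its percentage and leaves the count for later. The retention target is itself a percentage, which puts 51/64 in Amber unless percentages are rounded to whole numbers, in which case 79.7% becomes 80%. Retention counts can only be illustrative once the number randomised differs from 64. The Green/Amber overlaps lie between adjacent bands that both leave a full trial open. Amber against Red arises only at 38, which is very unlikely for retention if the true rate is near the planned 80%. The trial is descriptive, and no sample size, estimate or interval is affected.

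Much of this is fair, and it limits how serious the point is. It does not remove it. That the percentage governs is an inference and is written nowhere. The recruitment and Trust targets are stated as counts, which points the other way for those rows. The retention target settles the Green line for retention, but by contradicting the printed Green count, and it does not touch the 60% line or the Trusts row. Rounding to whole percentages does not rescue 6 of 8 Trusts, which is exactly 75%. That retention counts fail at other totals is a further reason to name the governing form.

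**Conclusion.** The concern holds. Table 2's count and percentage cut-offs disagree at four results: 51 retained, 38 retained, 38 recruited and 6 Trusts. A fifth entry, 64 in the Amber recruitment band, is a misprint for 63. These are decision thresholds for the primary outcome, so the error is more than typographical, although each conflict is only one participant or one Trust wide. It should be corrected.

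The most plausible place for it to matter is 51 of 64 retained: 12.3% at true retention of 80%, 8.3% at 75% and 6.4% at 85%. The most consequential place is 38, where Amber and Red are opposed; for retention that is likely only if the true rate is close to 60% (10.1% at 60%, 0.008% at 80%). These probabilities assume exactly 64 randomised and independent binomial retention, and percentages compared without rounding.

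**What to change.** Restate Table 2 with one non-overlapping rule per row:

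- **Recruitment:** Green 64 or more; Amber 39–63; Red 38 or fewer.
- **Retention:** the percentage of those randomised governs. Green 80% or more; Amber 60% to under 80%; Red under 60%. Counts are shown only as an illustration at 64 randomised: 52 or more, 39–51, 38 or fewer.
- **Trusts:** Green 7–8; Amber 5–6; Red 4 or fewer. If 6 was meant to be Green, set the Green cut-off at 75% and make Amber 5 only. The document does not show which was intended, so the sponsor has to choose.
- **Carbon monoxide (wording only):** Green 75% or more; Amber 50% to under 75%; Red under 50%. The row's target already places 75% in Green.

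The cost is the wording of one table. A boundary result may be graded slightly less favourably than the printed counts allow. The Trial status section describes the trial as ongoing, and the protocol says that amendments will be approved, so the change should go through that route and be dated before the results are compared with the criteria.
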